## Abstract

**Background:**

Osteoarthritis (OA) is a chronic degenerative joint disorder for which there is no known cure. Non-surgical management for people with mild-to-moderate hip OA focuses mainly on alleviating pain and maximising function via the National Institute for Health and Care Excellence (NICE) recommended combination of education and advice, exercise, and, where appropriate, weight loss. The CHAIN (Cycling against Hip pAIN) intervention is a group cycling and education intervention conceived as a way of implementing the NICE guidance.

**Methods:**

**C**yc**L**ing and **E**duc**AT**ion (CLEAT) is a pragmatic, two parallel arm, randomised controlled trial comparing CHAIN with standard physiotherapy care for the treatment of mild-to-moderate hip OA. We will recruit 256 participants referred to the local NHS physiotherapy department over a 24-month recruitment period. Participants diagnosed with hip OA according to NICE guidance and meeting the criteria for GP exercise referral will be eligible to participate. Primary outcome is the difference in Hip Disability and Osteoarthritis Outcome Score (HOOS) function, daily living subscale between those receiving CHAIN and standard physiotherapy care. Secondary outcomes include performance-based functional measures (40 m walking, 30s chair stand and stair climb tests), ability for patient to self-care (patient activation measure) and self-reported health-related resource use including primary and secondary care contacts. The primary economic endpoint is the number of quality adjusted life years (QALYs) at 24 weeks follow-up. The study is funded by the National Institute for Health Research, Research for Patient Benefit PB-PG-0816-20033.

**Discussion:**

The literature identifies a lack of high-quality trials which inform on the content and design of education and exercise in the treatment of patients with hip OA and explore cost-effectiveness. CLEAT is a pragmatic trial which seeks to build further evidence of the clinical benefits of the CHAIN intervention compared to standard physiotherapy care within a randomised, controlled trial setting, and examine its cost-effectiveness.

**Trial registration number:**

ISRCTN19778222. Protocol v4.1, 24th October 2022.

**Supplementary Information:**

The online version contains supplementary material available at 10.1186/s12891-023-06456-0.

## Background

Osteoarthritis (OA) is a long-term health condition for which there is no cure. Mechanical and systemic factors may result in joint pain leading to a reduction in quality of life and activities of daily living [1]. Data collected between 2003 and 2010 revealed that around 8.75 million people aged 45 years and over sought treatment for OA in the UK [2]. A 2017 assessment of the prevalence of joint-specific OA revealed that the hip is the second most common joint to be affected after the knee [3]. The Musculoskeletal Calculator estimates that in England 10.9% of people aged 45 years and over have hip OA [2, 4]. Although the risk of developing OA increases with age, a study of trends in incidence of OA between 2012 and 2018 showed a significant increase in the incidence of younger patients with hip OA [5].

Given its prevalence, OA represents a significant economic burden, due to the impact on people’s ability to work and their need for social care and welfare benefits as well as on-going healthcare [6]. According to the National Institute for Health and Care Excellence (NICE) guidelines [7], non-surgical management for people with mild-to-moderate hip OA involves education and advice, exercise (aerobic and local muscle strengthening), and, where appropriate, weight loss. The NICE guidelines do not, however, advise on specific types of exercise, exercise dose, or exercise intensity [7].

A systematic and network meta-analysis review concluded that low impact single exercise interventions, such as aerobic exercise (e.g., swimming, cycling), were the most effective therapies for improving pain and function in hip OA [8]. Indeed, Goh et al. found that therapies consisting of mixed exercises were the least effective in improving pain and function. However, several systematic reviews have highlighted the need for further research into more intense, single-exercise interventions specifically for hip OA [8–11].

A review of potential mechanisms underpinning the benefits of exercise therapy on pain and function in OA found that an increase in upper leg strength, a decrease of extension impairments, and an improvement in proprioception, were all possible mediators of the link between exercise and a decrease in OA symptoms in the lower limb; another review highlighted the need to address muscle weakness in people with hip OA [12, 13]. Cycling has been found to improve balance and proprioception, induce muscle hypertrophy, directly improve muscle weakness and therefore upper leg strength, and (because it is non-weight-bearing) causes less stress on the joints than running or other impact sport [14–16]. Additionally, longitudinal epidemiological studies [17] have shown that cycling can increase cardiorespiratory fitness and functional ability, and lead to significant risk reduction for all-cause and cancer mortality, cardiovascular disease, colon and breast cancer, and obesity morbidity in the middle-aged and elderly.

As a way of implementing the NICE guidelines for hip OA, a cycling and education intervention, the CHAIN (Cycling against Hip pAIN) programme, was developed in 2013 through discussions with local orthopaedic teams and physiotherapists [18] and was updated following feedback from past CHAIN participants. The CHAIN intervention aims to equip participants with the confidence to self-manage their condition, to encourage joint mobility and reduce pain through an 8-week programme of education and static cycling sessions [18–20]. The intervention has been designed to influence behaviour change and includes components to motivate, increase adherence, and reduce drop-out of participants.

### Aim and objectives

The primary clinical objective is to determine whether there is a difference in the change in self-reported function from baseline to post-treatment assessment between those receiving the 8 weeks cycling and education intervention compared to those who received routine physiotherapy care. Self-reported function is assessed using the Hip Disability and Osteoarthritis Outcome Score (HOOS) function, daily living subscale [21]. The primary economic endpoint is the cost per Quality-Adjusted Life Year (QALY) at 3 months post treatment.

The secondary objectives are to estimate cost-effectiveness of the CHAIN intervention by comparing health-resource use of the participants on the two arms of the study through completion of a questionnaire; and to compare changes between the groups in:

Self-reported level of hip pain assessed with the Pain subscale of the Hip Disability and Osteoarthritis Outcome Scale (HOOS) [21].Performance assessments: 40 m walking test, 30s chair stand test, Stair Climb test [22].Function level in performing five important activities they have difficulty with, assessed by the Patient-Specific Functional Scale [23] Participants identify up to five important activities they have difficulty performing and rate their current level of difficulty on a scale of 0 to 10.Participant’s knowledge, skill, and confidence to manage their own health assessed using the Patient Activation Measure questionnaire [24].Quality of life assessed with the EQ-5D-5 L and EQ-5D VAS questionnaire [25].

Data will be collected within two weeks of those on the CHAIN intervention arm completing their treatment and collected by post/email or telephone at 3 months post-treatment (with the exception of the objective function assessments).

## Methods

This pragmatic trial follows a successful feasibility study of the intervention [18, 19] and a case study of a participant in that study [26], which demonstrated that patients with complex comorbidities (such as ankylosing spondylitis, hypertension, type 2 diabetes, Crohn’s disease, gallstones, mild asthma, and bronchitis) are able to safely take part and benefit from the programme.

A flow diagram showing the design of this trial is shown in Fig. 1 and the schedule of assessments is presented in Table 1.

**Fig. 1 Fig1:**
[figure not shown]
CLEAT Trial flow diagram showing study design

### Trial design, setting and oversight

CLEAT is a pragmatic, two parallel arm, randomised controlled trial comparing a cycling and education intervention (CHAIN) with standard physiotherapy care reflecting standard practice in the National Health Service (NHS) in the UK [27]. The protocol has been developed with consideration of the recommendations for the minimum content of a clinical trial protocol as described in the SPIRIT 2013 statement [28].

This trial is open to patients who are referred to the NHS Physiotherapy Department with hip pain. For participants in the intervention arm, the trial will be conducted at a leisure centre, which was involved in the feasibility study. Participants in the (standard physiotherapy care) control arm, will be treated by the NHS Physiotherapy team they have been referred to.

**Table 1 Tab1:** SPIRIT^*^ diagram of enrolment, treatment, and assessments for the CLEAT study

Timepoint	Visit 1: Verbal consent and pre-baseline	Visits 1 and 2 may be combined Visit 2: Baseline (≤ 2 weeks prior to start of treatment)	Visit 3: Treatment	Visit 4: Post treatment (≤ 2 weeks after end of 8 weeks treatment period)	Visit 5: Long term follow-up (3 months post Visit 4 (± 4 weeks))
**Enrolment:**					
Eligibility screening (including medical history)		X			
Informed Consent	X verbal	X written			
Randomisation		X			
**Interventions**:					
CHAIN			X		
Standard care physiotherapy			X		
**Assessments**:					
Primary outcome					
^**†**^HOOS (function, daily living)		X		X	
Secondary outcomes					
HOOS (function, daily living)		X			X
HOOS (other subscales)		X		X	X
^**‡**^PAM		X		X	X
30-sec sit-stand test		X		X	
Stair climb test		X		X	
40 m walk test		X		X	
^**§**^BMI, % body fat, ^**¶**^BP,		X		X	
resting ^**#**^HR					
Analgesia Use (**RUQ)		X		X	X
Other measures					
Psychological questionnaire and patient feedback (CHAIN arm only)				X	
Interaction with CHAIN video content			X		
Range of motion of hip		X		X	
^**††**^PSFS		X		X	X
Exercise Diary			X		
Adverse Events		X	X	X	
Descriptive measures					
Age, gender, employment status, ethnicity, education		X			
Health economic data					
EQ-5D-5 L		X		X	X
RUQ		X		X	X

*Standard Protocol Items: Recommendations for Interventional Trials (SPIRIT); ^†^Hip Disability and Osteoarthritis Outcome Score (HOOS); ^‡^Patient Activation Measure (PAM); ^§^Body Mass Index (BMI); ^¶^Blood Pressure (BP); ^#^Heart Rate (HR); **Resource Use Questionnaire (RUQ); ^††^Patient-Specific Functional Scale (PSFS)

### Participants

We intend to recruit participants with hip pain or hip OA. OA will be diagnosed by a clinician using the NICE criteria [29] to review medical history and current symptoms. NICE recommend that OA is diagnosed if a person is 45 or over; has activity-related joint pain; and has either no morning stiffness or morning stiffness that lasts no longer than 30 min. An x-ray will not be required to confirm the diagnosis unless the participant is aged under 45. Eligibility criteria can be found in Table 2.

**Table 2 Tab2:** Eligibility Criteria for the CLEAT study

Inclusion Criteria	Exclusion Criteria
Male and female aged 18 years and over. If under 45, an x-ray confirming diagnosis of osteoarthritis is required. *	Hip surgery within the last 6 months
Diagnosed with osteoarthritis of the hip as per NICE criteria	On the waiting list for a hip replacement or planning back or lower limb surgery in the next 9 months
Meeting the GP criteria for exercise referral (British Heart Foundation 2010)	Current or past (within 3 months) intra-articular corticosteroid injection (or other injection) of the hip*
Capable of giving informed consent	Women who are pregnant and have not previously or are not currently exercising regularly to the equivalent of 30 min of static cycling per week
Willing to commit to the exercise intervention if randomised to the treatment arm	Judged by investigator to have high levels of functional limitations which will prevent the participant from getting on and off the exercise bike
Able to commit to the exercise intervention if randomised to the treatment arm as assessed by the physiotherapist after reviewing participant medical records at the baseline assessment	Due to the safety limitations of static bikes used, participants need to be ≥ 150 cm tall and weight ≤ 135 kg.
Be able to understand English as necessary to benefit from the intervention, in the investigator’s opinion	

*Eligibility criteria amended (Amendment 2, 25th April 2021 and Amendment 4, 7th October 2022) after discussion with the Trial Steering Committee to increase recruitment rates. Previously participants had to be aged 45 or over and were ineligible if had current or past (within 3 months) oral or intra-articular corticosteroid use

### Recruitment

Potential participants will be identified from Physiotherapy waiting lists by senior physiotherapists and screened by the research team as per exclusion criteria (Table 2). Eligible participants will be contacted by telephone (or by letter if unable to contact by telephone) by a senior physiotherapist to introduce the study. If interested in receiving more information, an invitation letter and participant information sheet (see supplementary files 1 and 2), will be sent by post. Eligible participants will receive a further telephone call a few days later to discuss the trial and answer any questions. If the participant is interested, they will be added to a waiting list. Once up to 30 participants are on the waiting list they will be invited for final screening and baseline assessment. Physiotherapy referral rates indicate that it will take less than 10 weeks to recruit 30 participants, which is less than the current waiting time for routine appointments at the trial site (currently 52 weeks).

### Pre-baseline and baseline (visits 1 and 2)

Prior to the baseline visit, the Trial Manager will contact participants by telephone to discuss the trial, offer participation and receive verbal informed consent (supplementary file 3). It will be explained that participation is voluntary, and they can withdraw at any time. During the telephone appointment, once verbal consent has been received, baseline data collection can commence.

Baseline assessments (Visit 2) will take place on the same day as randomisation. The participant will be asked to sign the informed consent form by the trial manager, or a delegated member of the research team, and the remaining baseline data will be collected by the trial assessors (see the Outcome measures section) and will include a review of participants’ medical history; physical measurements such as height, weight, body composition (measured with an electronic segmental body composition monitor (Tanita MC-780MA Multi Frequency Body Composition Analyser https://fitech.uk/medical-class-scale-systems/47-tanita-mc-780ma-s-multi-frequency-body-comp-analyser-portable.html), blood pressure, resting heart rate and range of motion of both hips. Performance assessments as recommended by the Osteoarthritis Research Society International (OARSI) for core performance tests will be collected [22] :30 s chair stand test, stair climb test and 40 m walk test. Patient reported outcome measures will be collected through validated questionnaires: the HOOS [21]; the EQ-5D-5 L and EQ-5D VAS [25]; the Patient-Specific Functional Scale [23] and the Patient Activation Measure [24}.

Assessments will be undertaken by qualified independent physiotherapists who have been trained by the trial investigators. A summary of the data to be collected at Baseline can be found in Table 1.

As part of baseline assessments, participants will also be asked to do an exercise tolerance test which involves riding a static cycle for up to 18 min, with heart rate, blood pressure and exertion rates tested at intervals. Any participant outside the expected parameters for these tests and judged by the physiotherapist assessors to be unfit for the cycling intervention, or anyone not wishing to take part in the cycling and education intervention, will not continue the study. Participants are enrolled on the study after baseline assessments have been completed and they have been randomised to receive either the CHAIN intervention or standard physiotherapy treatment. It is possible for Visit 1 and Visit 2 to be carried out on the same day as part of the baseline assessment. Treatment will commence within the following two weeks for both arms.

### Randomisation

Participants will be randomised using permuted blocks of size 2, 4 or 6 with parallel group randomisation in a 1:1 ratio to either CHAIN or standard physiotherapy treatment. Ideally the CHAIN intervention is run with 15 participants, so recruitment will be based on blocks of 30 eligible participants. However, the programme can proceed with fewer participants if necessary to prevent undue delays in treatment. With the use of block randomisation, we hope to achieve equal numbers of participants in each arm of the trial while maintaining treatment allocation concealment from the trial assessors.

A list of randomised allocations will be created for the whole study prior to the first person being recruited.

Once consent has been received and screening/baseline assessments completed, the trial manager (or delegated person) will randomise the participant, using the randomisation system incorporated within the trial database, to receive the next treatment allocation from the randomised list. If a participant does not complete the screening/baseline procedures or meet the required eligibility criteria, they will not be randomised and will be removed from further involvement with the study.

Assessors undertaking assessments at baseline and follow-up will be blinded to the randomisation, and participants will be educated to ensure that they do not inform the assessors of which treatment arm they participated in. The nature of the intervention means that participants and treatment providers will not be blinded.

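### One role may offer participation, take consent and draw the next allocation from a single small-block list, so on the baseline day a running tally predicts the next arm about 70% of the time

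*Protocol article*

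**What the plan says.** - Allocation method (Randomisation): "Participants will be randomised using permuted blocks of size 2, 4 or 6 with parallel group randomisation in a 1:1 ratio". Also: "A list of randomised allocations will be created for the whole study prior to the first person being recruited". No stratification factor is named, and the Discussion says the trial runs at a single site.
- Who allocates (Randomisation): after consent and baseline, "the trial manager (or delegated person) will randomise the participant, using the randomisation system incorporated within the trial database".
- Who offers participation and takes verbal consent (Pre-baseline and baseline): "the Trial Manager will contact participants by telephone to discuss the trial, offer participation and receive verbal informed consent".
- Who takes written consent, on the day of randomisation (same section): "The participant will be asked to sign the informed consent form by the trial manager, or a delegated member of the research team". Visits 1 and 2 may fall on the same day.
- Blinding (Randomisation): "The nature of the intervention means that participants and treatment providers will not be blinded". Assessors are blinded at baseline and follow-up, and allocation concealment is mentioned only in relation to them.
- First approach (Recruitment): "Eligible participants will be contacted by telephone (or by letter if unable to contact by telephone) by a senior physiotherapist to introduce the study".
- Cohorts (Recruitment): "Once up to 30 participants are on the waiting list they will be invited for final screening and baseline assessment".

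**The concern.** Concealment has to protect against the people who decide, or can influence, who is randomised next. Here the one role named in all three steps (offer, consent, allocation) belongs to someone who is not an assessor, and nothing in the text separates the steps. The trial is open and there is one unbroken sequence, so anyone who learns each arm as it is drawn can keep a tally. Small blocks force the arms back to balance every 2 to 6 people, which makes the tally informative.

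What is at stake is selection before randomisation. The primary outcome is self-reported function in an unblinded comparison. Entry requires willingness to commit to the exercise programme, and people who do not want it leave before randomisation. A consent conversation can influence both. The planned adjustment for baseline function and CHAIN group would not fully capture differences in motivation or expectation.

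**Working it through.** The protocol gives no predictability figure to reproduce. The inputs are the block sizes 2, 4 and 6, the 1:1 ratio, the single list and the recruitment target of 256. That target itself reproduces: 102/0.8 = 127.5, so 128 per arm and 256 in total.

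**1. Guessing the very next assignment.** The rule is to guess the arm that is behind and toss a coin when the arms are level. In a block of 2m the expected number of correct guesses is m + (2^(2m)/C(2m,m) − 1)/2.
- Block of 2: 1 + (4/2 − 1)/2 = 1.5, or 75.0%.
- Block of 4: 2 + (16/6 − 1)/2 = 2.833, or 70.8%.
- Block of 6: 3 + (64/20 − 1)/2 = 4.1, or 68.3%.

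The mix of sizes is not stated. If each size is equally likely per block (assumption): (1.5 + 2.833 + 4.1)/12 = 8.433/12 = 70.3%. Over any mix the range is 68.3% to 75.0%. Against chance, 0.203 × 256 is about 52 extra correct guesses.

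**2. Are block boundaries needed?** No. In 400 simulated lists of 256, an optimal guesser who knew the sizes but not the boundaries scored 70.1%, the same as simply guessing the arm that is behind. About 4% of assignments could be known with certainty.

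**3. How often is the tally silent?** The expected number of assignments made with the arms level is 1 in a block of 2, 1.667 in a block of 4 and 2.2 in a block of 6. With equally likely sizes: 4.867/12 = 40.6%. In the other 59.4% the guess is right (70.3 − 0.5 × 40.6)/59.4 = 84% of the time.

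**4. What if others are randomised between the guess and the allocation?** This was simulated with 3,000 lists of 256, equally likely sizes and the same rule:

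| People randomised in between | Correct guesses |
|---|---|
| 0 | 70% |
| 1 | 58% |
| 3 | 52% |
| 5 | 50% |

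**5. Where does this apply in the trial?** At an earlier telephone call, with up to 30 people on the waiting list, several others may be randomised first and little prediction is left. On the baseline day, written consent and allocation happen together, and the offer too if Visits 1 and 2 are combined. That is where the 70% applies.

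**6. Would larger blocks cure it?** For sizes 4, 6, 8 and 10 the same formula gives 2.833 + 4.1 + 5.329 + 6.532 = 18.794, and 18.794/28 = 67%. If a whole cohort is allocated together after its baselines are locked, or if those who offer and consent cannot see past allocations, the rate is 50%.

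**The case against.** The case on the other side has substance.

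- The trial manager's discretion is narrow. Senior physiotherapists identify and first approach patients, blinded assessors judge fitness, and a physiotherapist assesses ability to commit. No passage gives the trial manager the judgement about understanding English. This stands. What remains is persuasion during the offer and consent, and the order in which people are randomised.
- There are real safeguards: a list made in advance, release by a system inside an independently run database, and release only after consent and baseline. These stop anyone from reading or altering the next entry. They do not stop inference from past entries.
- A reader might infer that the trial manager sees every past allocation. The document does not say so. A delegate may randomise some participants, and viewing rights are not described in the article. The point is that the text permits one role to do all three tasks and states no barrier.
- A reader might apply the 70% to the whole of recruitment, including the first telephone call. The fall to 58% and 52% shows that this is wrong.
- A reader might think that mixing sizes fails because blocks of 2 dominate. With equally likely sizes, blocks of 2 hold only 2/12 (17%) of participants and blocks of 6 hold half.

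**Conclusion.** The concern holds in a limited form. Consent and allocation may rest with the same role in an open, single-site trial with one small-block list, and stated concealment does not reach that role. The next assignment is predictable at about 70% (68% to 75%), assuming that every earlier allocation is known and nobody is randomised in between. The exposure lies mainly on the baseline day.

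It is tempting to convert this into a bias or an inflated false-positive rate. That would need the prognostic difference between people steered towards each arm, and the document supports no value for it. Any such figure would only be illustrative, and the size of the bias cannot be computed. Nothing here alleges that steering has occurred, and the sample size calculation is not affected. This is an inexpensive improvement that is worth making.

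**What to change.** **Main change (Randomisation section).** State that the delegated person already allowed for operates the randomisation system and takes no part in offering participation, taking consent or scheduling. State also that those who do these tasks cannot view the running allocations. The Control arm section has first appointments given at the baseline visit, so the same delegate would best tell participants their arm and pass these on. Cost: some reassignment of tasks within the existing team, and no extra patients. For participants already randomised, report who took consent and who randomised.

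**Minor addition.** Drop block size 2. Sizes 4, 6, 8 and 10 bring guessing only to about 67%, so this does not replace the separation of roles.

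**Option.** Release each cohort's allocations together once all its baselines are locked, which brings guessing to 50%. Besides the Randomisation section, this needs matching edits to the Pre-baseline and baseline section (randomisation on the baseline day) and the Control arm section (appointment given at the baseline visit). It is feasible only if it fits the two-week window for starting treatment. Participants would learn their arm a few days later.
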